### Laboratory analysis

The examination of blood and aqueous humor samples will be conducted at the Pharmacology Laboratory, Faculty of Medicine, Universitas Indonesia (FMUI). Blood samples will be collected from all study participants who will have provided written informed consent. The collection, storage, and transportation procedures will be carried out under strict control of time and temperature to maintain sample stability. All participants will be gathered at the same time, and blood samples will be collected sequentially within a short period so that the entire process, from the first to the last sample, will be completed within one hour.

Immediately after collection, blood samples will be temporarily stored in a cooler box and will be transported from Sayang General Hospital, Cianjur, to the Pharmacology Laboratory, FMUI, under police escort from the Cianjur Police Department. The total transport time will be less than two hours. Centrifugation will be performed within six hours after collection at a speed of 1,000G for 15 minutes to obtain plasma, will be then stored at −80°C until further analysis.

Participants will be randomly assigned into three groups using computer-generated randomization: one placebo group and two intervention groups receiving oral vitamin C supplementation at predetermined doses. Each participant will be provided with a logbook containing the follow-up schedule, adverse effect monitoring, and contact information in case of any complaints. A second blood sample will be collected after seven days of supplementation for the analysis of ascorbic acid (AA), total antioxidant capacity (TAC), and malondialdehyde (MDA).

Aqueous humor samples will be collected twice, each of 0.2 mL: first, immediately after the incision (pre-phacoemulsification), and second, three minutes after viscoelastic removal following intraocular lens implantation (post-phacoemulsification). Both aqueous humor samples will be stored in a cool box containing dry ice at −78°C and will subsequently be transferred to long-term storage at −80°C in the Pharmacology Laboratory, FMUI, before analysis.

Principles of Analysis:
1.Measurement of Ascorbic Acid (AA) Levels
Ascorbic acid levels will be determined using an Enzyme-Linked Immunosorbent Assay (ELISA) Kit for Vitamin C (Cat. No. CEA913Ge). The principle of this assay is based on a competitive inhibition enzyme immunoassay method.2.Measurement of Total Antioxidant Capacity (TAC)
Total antioxidant capacity will be measured using the QuantiChrom™ Antioxidant Assay Kit (DTAC-100, BioAssay Systems). This assay is based on the cupric ion reducing antioxidant capacity (CUPRAC) method.3.Measurement of Malondialdehyde (MDA) Levels
•MDA in Aqueous Humor:
Malondialdehyde levels in aqueous humor will be determined using a Malondialdehyde ELISA Kit (ab287797, Abcam). The principle of this assay is based on an indirect sandwich enzyme-linked immunosorbent assay (ELISA) for the quantitative detection of MDA in serum, plasma, or other biological fluids.•MDA in Blood Samples:
Malondialdehyde levels in blood samples will be measured using a spectrophotometric method based on the reaction of MDA with thiobarbituric acid (TBA) to form a pink-colored complex that can be quantified spectrophotometrically.

### Participant compensation

Participants receive IDR100,000 at the end of the last follow-up.

### Statistical analysis

Data from this study will be recorded and analyzed by IBM SPSS 20.0. Sample personal identification, including demographic and clinical characteristics, will be reported in a descriptive analysis. Data distribution of numerical variables will be assessed using the Shapiro–Wilk test with normal distribution will be presented as mean (standard deviation [SD]); non-normal distribution will be reported as median (interquartile range [IQR]). Nominal data will be reported in frequency and percentage. We will use Pearson’s chi-squared test for categorical data. For comparisons among the three groups, one-way ANOVA will be used for normally distributed data, while the Kruskal–Wallis test will be used for non-normally distributed data. Significant group differences will be followed by post-hoc pairwise comparisons using Bonferroni correction for ANOVA or Dunn’s test following the Kruskal–Wallis analysis to account for multiple testing. Pearson’s test will be used to test the correlation between data in aqueous humor and serum. A p-value of less than 0.05 (p < 0.05) will be considered statistically significant.

Effective phacoemulsification time (EPT) and total surgical duration will be included as covariates in the statistical analysis to account for their potential influence on postoperative endothelial outcomes. Multivariable analysis will also be conducted to control for potential confounding variables, including smoking status, occupational exposure, ultraviolet (UV) light exposure, and dietary intake of vitamin C. These variables will be collected through structured questionnaires during the screening.

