### Aims

The aim of this study is to analyze the protective effect of oral ascorbic acid supplementation on corneal endothelial cells which undergo oxidative stress due to phacoemulsification in patients with hard nucleus cataracts. The primary outcome will investigate mean change and percentage in endothelial cell density (ECD) loss prior to and after phacoemulsification, assessed at postoperative follow-up period (day 1, week 1, week 4, and week 6) of patients with hard nucleus cataracts.

The secondary endpoint will investigate mean change in other clinical parameters such as central corneal thickness (CCT), visual acuity, and cells in the anterior chamber during the postoperative follow-up period. This study will investigate differences in MDA levels in aqueous humor, prior to and after phacoemulsification, and compare between groups with vitamin C supplementation and those without. We will also investigate differences in AA, TAC, and MDA levels in serum and aqueous humor at the start of the study and after seven days of supplementation and compare them between the three groups. Furthermore, we will explore the correlation between aqueous humor and serum AA, TAC, and MDA levels.

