### Screening

We screen patients who sign up for a mass cataract surgery event in a regional hospital in Cianjur, West Java, Indonesia. Patients will be asked for information regarding personal identification, history of systemic and ocular diseases, and allergies. They then will undergo ophthalmology examination including uncorrected visual acuity (UCVA) and best corrected visual acuity (BCVA), intraocular pressure using non-contact tonometry (NCT), biomicroscopy slit lamp, and indirect fundoscopy to evaluate anterior and posterior chambers. Lens opacity will then be measured using LOCS III criteria. We will also examine ECD, coefficient of variety (COV), and hexagonality of endothelial cell layers using a specular microscope (REM 4000, Rodenstock, Germany), central corneal thickness (CCT) using Anterior Segment Optical Coherence Tomography (ASOCT), and biometry. Blood samples will be then drawn from patients to measure serum AA, MDA, and TAC.

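### The ECD comparison is a covariate-free test picked by Shapiro–Wilk; the named covariates omit baseline ECD and nuclear grade but include two measured at surgery.

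*Protocol article*

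**What the plan says.** All references are to the protocol article.

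- **Aims**: "The primary outcome will investigate mean change and percentage in endothelial cell density (ECD) loss prior to and after phacoemulsification". The visits are day 1 and weeks 1, 4 and 6.
- **Sample size calculation**: built on a difference of 132 cells/mm² in ECD loss with SD 201, which is a difference in means.
- **Screening**: "We will also examine ECD, coefficient of variety (COV), and hexagonality of endothelial cell layers using a specular microscope". Lens opacity is graded by LOCS III at the same visit. The Participants section admits nuclear grades 4 to 6, so grade varies within the trial.
- **Statistical analysis, first paragraph**: "Data distribution of numerical variables will be assessed using the Shapiro–Wilk test". On the outcome of that check, the section goes on: "For comparisons among the three groups, one-way ANOVA will be used for normally distributed data". If normality is rejected, Kruskal–Wallis takes over. The follow-up step reads: "Significant group differences will be followed by post-hoc pairwise comparisons using Bonferroni correction for ANOVA or Dunn’s test".
- **Statistical analysis, second paragraph**: "Effective phacoemulsification time (EPT) and total surgical duration will be included as covariates in the statistical analysis". A multivariable analysis is added for smoking, occupational exposure, UV exposure and dietary vitamin C, all taken from screening questionnaires. No model is named for any of these covariates.
- **Intervention** and **Post-intervention evaluation**: allocated treatment starts one week before surgery; EPT and surgical duration are recorded at surgery.

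**The concern.** Three choices that the article itself makes weaken the main comparison.

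1. **The quantity estimated depends on a pretest.** If Shapiro–Wilk rejects, the plan reports medians and a rank test. The aim is a mean change and the sample size rests on a mean difference, so the headline result may not address either. With four visits and two scales (change and percentage), the test may also differ from one result to the next.
2. **The most obvious baseline covariates are not on the list.** Baseline ECD is the same measurement as the outcome, taken earlier. The Introduction itself links hard nuclei to longer, higher-power phacoemulsification and a higher risk of decompensation, yet nuclear grade is not named either.
3. **Two of the covariates are measured after randomisation.** A main treatment estimate adjusted for EPT and duration conditions on events that follow a week of allocated treatment, and loses the plain protection of randomisation. Nuclear grade, measured beforehand, is likely to carry part of the same prognostic information without that difficulty.

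At stake are precision, the interpretability of the estimate, and a choice among unadjusted, EPT-adjusted and multivariable results once the data are visible.

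**Working it through.** **1. The plan's own sample size.** Inputs from Sample size calculation: difference 132, SD 201 (taken as the SD of ECD loss), α = 0.05 (two-sided assumed), power 80%.

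n per group = 2 × [201 × (1.960 + 0.842) / 132]² = 36.40.

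The stated 36 reproduces to rounding. With the 10% allowance, 36 / 0.9 = 40, also as stated. The sizing is for an unadjusted two-group mean comparison.

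**2. When each named covariate is measured.**

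| Covariate | Measured |
|---|---|
| EPT | At surgery, after one week of allocated treatment |
| Total surgical duration | At surgery, after one week of allocated treatment |
| Smoking | Screening |
| Occupational exposure | Screening |
| UV exposure | Screening |
| Dietary vitamin C | Screening |
| *Baseline ECD (not named)* | Screening |
| *LOCS III nuclear grade (not named)* | Screening |

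So 2 of 6 are post-randomisation and 4 of 6 are baseline.

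**3. What adjusting for baseline ECD gains.** Let s² be the ECD variance, assumed equal before and after surgery, and r the correlation between baseline and postoperative ECD at one visit.

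- Change score: variance 2s²(1 − r).
- ANCOVA: residual variance s²(1 − r²).
- Ratio: (1 − r²) / [2(1 − r)] = (1 + r)/2.

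The effective SD is then 201 × √[(1 + r)/2]. Power is from the noncentral t distribution for one pairwise comparison, 36 per group, two-sided 0.05, difference 132.

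| r (assumed) | Variance ratio | Effective SD | Power |
|---|---|---|---|
| no adjustment | 1.00 | 201.0 | 78.5% |
| 0.9 | 0.95 | 195.9 | 80.5% |
| 0.7 | 0.85 | 185.3 | 84.6% |
| 0.5 | 0.75 | 174.1 | 88.7% |

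In patient numbers this is worth 1/0.95 = 1.05 to 1/0.75 = 1.33, or 5% to 33% more patients. The formula does not apply to percentage loss, and any further gain from nuclear grade cannot be computed from the article.

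**4. Does the pretest inflate type I error?** The Shapiro–Wilk rule was simulated with three groups of 36 and 8,000 runs per scenario. Type I error was 4.9% with normal data and 4.9% with skewed data (lognormal, sigma 0.6) of the same shape in every group. No inflation appeared. The cost is that the quantity estimated is not fixed in advance.

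**The case against.** The strongest replies, and what stands of each:

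- **Baseline ECD is already used.** A reader might infer that the plan ignores it. It does not: change and percentage loss both contain it. But subtraction fixes the baseline coefficient at one instead of estimating it, so a chance imbalance is handled only in part and precision is given away. The supportable statement is that baseline ECD is not a covariate.
- **Most covariates are harmless.** A reader might infer that the list is mainly post-randomisation. It is two of six. Calling the four questionnaire variables confounders is loose language in a randomised trial, but adjusting for them does not bias the treatment estimate.
- **EPT and duration may be unaffected by treatment.** Surgeons are blinded, machine and settings are standardised, and intraoperative complications are an exclusion, so it is hard to argue that duration stands in for complications. The article shows no route from oral vitamin C to EPT. This stands: no bias is demonstrated. The objection to these covariates is one of principle about the main estimate.
- **The two paragraphs are compatible.** A reader might infer a flat contradiction. The multivariable work is introduced as an additional analysis, and an unadjusted test followed by an adjusted model is coherent. A separate analysis plan may also say which is primary. The point therefore rests only on what the article fixes: the tests, the rule for choosing between them, and the covariate list.
- **The pretest does no damage to error rates.** Agreed for the scenarios simulated. With skewed data and a pure shift of 132 in one group, the rule even had more power than ANOVA (97.9% against 82.2%). That supports keeping a rank test as a sensitivity analysis; it does not supply a mean difference in cells/mm².

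**Conclusion.** The point holds as an improvement that should be made; it does not invalidate the design. The named comparison is covariate-free and selected by the data, the covariate list lacks the two baseline variables with the clearest claim, and it includes two that do not belong in the main treatment estimate.

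The measurable part is a 5% to 25% reduction in the variance of the change-score comparison. In power at 36 per group, that is from 78.5% to between 80.5% and 88.7%. It rests on r between 0.9 and 0.5, which the article does not give, and on equal variances before and after surgery. At the high end of r the gain is small.

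A reader might also infer that the trial misses its stated power on this account. It does not: the stated sample size reproduces without any adjustment. Any loss of power from Bonferroni-corrected pairwise tests is a separate matter.

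**What to change.** 1. Make the primary analysis an ANCOVA of postoperative ECD on randomised group, with baseline ECD and baseline LOCS III nuclear grade as covariates. The week-6 contrast of a mixed model over the four visits, with the same covariates, is an equivalent choice.
2. Report adjusted mean differences in cells/mm² with 95% CI whatever the Shapiro–Wilk result. Keep a rank-based comparison as a sensitivity analysis.
3. Move the models containing EPT, surgical duration and the four questionnaire variables to sensitivity analyses.

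**Cost:** no new data, since every variable is already collected, and slightly more analysis work. The article's Study status section places the trial in data processing at submission (September 2025), so the change must be documented and dated before unblinding. If unblinding has already happened, the report should say so and present the adjusted model as chosen afterwards.

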### Sample size calculation

A total sampling method was used. The sample size was determined based on the primary outcome of postoperative corneal endothelial cell density (ECD) loss, referring to a previous study by Chee et al.
^
14
^ The minimal sample size calculated for this study was 36 subjects for each group (95% confidence interval, power 80%, β = 0.20, α = 0.05, SD = 201 ​​cell/mm
^2^, expected difference = 132 ​​cell/mm
^2^, subjects should have at least 132 ​​cell/mm
^2^ difference of ECD loss after phacoemulsification in the intervention group). With a 10% additional for anticipating loss to follow-up subjects, the minimal sample size needed was 40 for each group.

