### Post-intervention evaluation

Patients will be asked to come a week after screening. Firstly, they asked the side effects of the supplementation, including gastrointestinal disorders (nausea, diarrhea, epigastric pain). Second blood samples will be then drawn to measure post-intervention serum AA, MDA, and TAC.

Sampling for oxidative stress in the aqueous humour will be performed twice, pre- and post-phacoemulsification. During surgery, after the initial incision, 0.2 mL of aqueous humor will be taken using a 1 cc syringe with a 30 G cannula. Phacoemulsification will then be conducted using standard operating procedure to intraocular lens implantation. Another 0.2 mL of aqueous humor will then be taken three minutes after removing the viscoelastic as a post-phacoemulsification sample. This sampling volume is within the range commonly used in aqueous humor biomarker studies and is considered safe under surgical conditions. Because the sampling will be performed through the surgical incision and the anterior chamber will subsequently be maintained with a balanced salt solution, anterior chamber stability will not be affected.
^
16,
17
^ The pre-phacoemulsification aqueous humour samples will be analysed for ascorbic acid (AA), total antioxidant capacity (TAC), and malondialdehyde (MDA), while the post-phacoemulsification samples will be analysed for MDA levels only. Intraoperative parameters, including effective phacoemulsification time (EPT) and total surgical duration, will be recorded for each procedure. All patients will receive topical medications: levofloxacin 5 mg/mL every three hours for one week, prednisolone acetate 10 mg/mL every three hours for 1 week, and tapered down in 4-6 weeks.

Every patient will be evaluated one day, one week, four weeks, and six weeks post-phacoemulsification to measure study parameters and signs of complications, i.e. inflammation or infection. Patients who experience side effects or complications, including toxic anterior segment syndrome (TASS) or endophthalmitis during the duration of follow-up will be exempted from the study and managed according to the standard operational procedure of the Department of Ophthalmology, Faculty of Medicine, University of Indonesia.

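### Serum AA, TAC and MDA have a pre-treatment value, but the stated three-group test leaves it out, which costs precision on these secondary endpoints

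*Protocol article*

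**What the plan says.** The Screening section sets the pre-treatment sample: "Blood samples will be then drawn from patients to measure serum AA, MDA, and TAC". The Post-intervention evaluation section sets the sample a week later, before surgery: "Second blood samples will be then drawn to measure post-intervention serum AA, MDA, and TAC".

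The Aims section lists as a further comparison, separate from the primary outcome, the "differences in AA, TAC, and MDA levels in serum and aqueous humor at the start of the study and after seven days of supplementation", to be compared between the three groups.

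The Statistical analysis section gives one rule for numerical outcomes: "For comparisons among the three groups, one-way ANOVA will be used for normally distributed data, while the Kruskal–Wallis test will be used for non-normally distributed", followed by Bonferroni or Dunn pairwise tests. It then names effective phacoemulsification time and surgical duration as covariates for the endothelial outcomes. It adds a multivariable analysis for confounders that include smoking, occupational exposure, UV exposure and dietary vitamin C. The screening value of the serum marker is in neither list.

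**The concern.** The trial collects, in every patient, what is likely to be a strong predictor of the day-7 serum value, namely the same marker before treatment. The stated test does not use it. The plan would adjust for diet reported by questionnaire but not for the measured starting level.

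The Aims wording most naturally means change from screening to day 7. A raw change score fixes the slope on baseline at 1. Where the true slope is below 1, this adds noise and over-corrects: an arm that happens to start lower will tend to show a larger rise. If the wording means day-7 levels instead, the baseline is discarded and the arm that starts higher tends to end higher.

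These comparisons bear on the hypothesis in the Introduction that oral vitamin C raises antioxidant levels and reduces oxidative damage. Lost precision matters most for TAC and MDA, where an effect may be modest.

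**Working it through.** **Inputs from the protocol.** There are 40 patients per group in three groups (Intervention). Groups 1 and 2 receive the same treatment up to day 7 (Intervention), so the day-7 contrast of vitamin C with placebo is 80 v 40. Alpha is 0.05, taken as two-sided.

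**Assumed.** The correlation rho between screening and day-7 values is 0.3 to 0.7, and the variance σ² is the same at both times. The protocol gives no serum SD, effect, correlation or power target.

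**The plan's own figure.** The sample size inputs are "95% confidence interval, power 80%, β = 0.20, α = 0.05, SD = 201" and "expected difference = 132" cells/mm². Then n = 2 × (201 × (1.960 + 0.842) / 132)² = 36.4 per group, against the stated 36. Adding 10% gives 36/0.9 = 40. The figure reproduces to within rounding, but it sizes endothelial cell density (ECD) loss. It says nothing about power for the serum markers.

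**Variance per patient.**
- Change score: 2σ²(1 − rho)
- Day-7 value only: σ²
- ANCOVA on screening value: σ²(1 − rho²)

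The ratio of ANCOVA to change score is therefore (1 + rho)/2, and of ANCOVA to day-7-only it is 1 − rho².

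**Power.** Take an effect that the unadjusted comparison detects with 80% power, so its standardised distance is 1.960 + 0.842 = 2.802. Divide by the square root of the variance ratio. For rho 0.5, 2.802/√0.75 = 3.235; 3.235 − 1.960 = 1.275, which is 89.9% power.

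| | rho 0.3 | rho 0.5 | rho 0.7 |
|---|---|---|---|
| Variance ratio v change score | 0.65 | 0.75 | 0.85 |
| 80% with change score becomes | 93.5% | 89.9% | 86.0% |
| 50% with change score becomes | 68.1% | 61.9% | 56.6% |
| Variance ratio v day-7 only | 0.91 | 0.75 | 0.51 |
| 80% with day-7 only becomes | 83.6% | 89.9% | 97.5% |

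Against change scores, the gain shrinks at high correlation: 80% becomes 84.0% at rho 0.8 and 82.0% at rho 0.9.

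**Chance imbalance.** A baseline difference D shifts the change-score contrast by −(1 − rho)D and a day-7-only contrast by +rho × D. For 80 v 40, the SE of D is √(1/80 + 1/40) = 0.194 SD, so a gap of 0.3 SD is 0.3/0.194 = 1.55 SE. At rho 0.5 it moves the change-score contrast by 0.3 × 0.5 = 0.15 SD. For a comparison of two single arms the SE is √(2/40) = 0.224 SD.

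**Simulation check, 40 per group.** At rho 0.3, 0.5 and 0.7, the slope of the change-score estimate on the imbalance was −0.689, −0.502 and −0.306. With ANCOVA it was 0.010, −0.003 and −0.007. The variance ratios were 0.657, 0.751 and 0.854, in line with the formula. The mean change-score contrast under no effect was between −0.0005 and 0.004, so there is no bias on average.

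**Unequal variances.** If the day-7 SD is k times the screening SD, the ratio to the change score is k²(1 − rho²)/(1 + k² − 2k·rho). For k = 0.8 it is 0.50 to 0.63 across rho 0.3 to 0.7; for k = 1.25 it is 0.78 to 0.98. ANCOVA stays below 1 in each case, but the size of the gain varies.

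**The case against.** **Nothing here is invalid.** A reader might infer that the planned test is biased or inflates the type I error. The documents do not support that. Allocation is randomised, so both a change-score and a day-7 comparison are unbiased on average, and a chance imbalance is already covered by the 5% level. What stands is lost efficiency, and a shift conditional on the imbalance actually observed.

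**The change-score analysis is inferred.** No section says that the ANOVA is run on serum changes. The Aims sentence covers serum and aqueous humor together, and aqueous humor is first sampled at surgery, so the sentence cannot define a change from study start for both. This is right, and the change score should not be reported as a stated fact. The loss remains on either reading, although its direction and its dependence on rho differ.

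**The covariate list is open.** The multivariable variables are introduced as examples, and the outcomes to be modelled are not stated. A fuller plan may add the screening value. Still, the test for three-group comparisons is fixed in the text, and it has no baseline term. Effective phacoemulsification time and surgical duration arise after the day-7 blood sample and cannot stand in for one.

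**The size is hypothetical.** The correlation and the starting powers are assumed, and the tabulated powers assume equal variances and one common correlation. If supplemented patients converge towards a plateau, as the dose rationale in the Intervention section might suggest for vitamin C itself, those assumptions fail, and that rationale does not extend to TAC or MDA. This stands as a limit on the figures. The unequal-variance check shows that it changes the size of the gain and does not reverse it.

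**Conclusion.** The point holds as a modest efficiency loss. Serum AA, TAC and MDA are each measured before treatment, and the stated between-group test does not use that value.

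For a correlation of 0.3 to 0.7 and equal variances, ANCOVA would have 0.65 to 0.85 of the variance of a change-score comparison, or 0.91 to 0.51 of that of a day-7-only comparison. The gain over change scores is small at high correlation. The gain on either reading is small for a marker whose effect is very large, which may be so for serum AA. The variance figures concern the ANOVA branch; the Kruskal–Wallis test equally has no baseline term, but its loss was not calculated.

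Two wider readings should be avoided. The point does not reach aqueous humor, which has no pre-treatment value to adjust for. It also does not touch the primary ECD conclusion, because the serum comparisons are secondary and mechanistic.

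**What to change.** In the Statistical analysis section, state that each serum marker (AA, TAC, MDA) will be analysed with a linear model of the day-7 value on treatment, with that marker's screening value as covariate, on the log scale if skewed. Report the adjusted difference between vitamin C (Groups 1 and 2 together, since they are treated alike to day 7) and placebo with its 95% confidence interval. Keep the raw changes as description.

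The cost is one sentence and one model per marker in the software already named, with no new samples or patients. The Study status section places the trial in data processing and does not say whether the groups have been unblinded. The change should be dated before unblinding or, if that has already happened, labelled post hoc.

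### Screening ECD is not among the named covariates for the primary ECD comparison; adding it would gain some precision at no cost in data

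*Protocol article*

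**What the plan says.** The Aims section of the protocol article defines the primary outcome as "mean change and percentage in endothelial cell density (ECD) loss prior to and after phacoemulsification", assessed at day 1 and weeks 1, 4 and 6 after surgery. No single visit is marked as primary. The Sample size calculation section is built on the same quantity: "The sample size was determined based on the primary outcome of postoperative corneal endothelial cell density (ECD) loss".

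The pre-operative count exists for every screened patient. Under Screening the article says "We will also examine ECD, coefficient of variety (COV), and hexagonality of endothelial cell layers", by specular microscopy.

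For the group comparison the Statistical analysis section says "For comparisons among the three groups, one-way ANOVA will be used for normally distributed data", and Kruskal–Wallis if the data are not normal. Neither test takes a covariate. The next paragraph adds covariates: "Effective phacoemulsification time (EPT) and total surgical duration will be included as covariates in the statistical analysis". It also plans a multivariable analysis for smoking, occupational exposure, UV exposure and dietary vitamin C. Screening ECD appears in neither place.

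**The concern.** Subtracting the screening count from the postoperative count fixes the coefficient of baseline at exactly 1. If the true coefficient is smaller, loss remains correlated with baseline. There are two ordinary reasons to expect this. Measurement error in the screening count enters the change score directly, and if loss is roughly proportional, eyes that start with more cells lose more.

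Two things follow. The variation in loss that baseline explains stays in the error term. And if the arms differ by chance in screening ECD, part of that difference appears in the estimated treatment effect. With 36 to 40 patients per arm and a sample size that sits almost exactly at its power target, a covariate already in hand is worth using.

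This is more than detail left to a fuller plan. The article commits to particular adjustment variables, two of them recorded only during surgery, and does not name the baseline value of the primary outcome.

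**Working it through.** **Inputs from the Sample size calculation section.** "power 80%, β = 0.20, α = 0.05", "expected difference = 132" cells/mm², SD 201 cells/mm², and 36 per group before a 10% dropout allowance. I take the test as two-sided and 201 as the SD of ECD loss; the article says neither outright.

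**The plan's own figure.** n per group = 2 × [201 × (1.960 + 0.842) / 132]² = 36.4, against the stated 36. With dropout, 36 / 0.9 = 40, as stated. Normal-approximation power at 36 is 79.6%. The t-based value, with standardised difference 132/201 = 0.657, is 78.5%. The planned size therefore fits an unadjusted two-group comparison of loss.

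**Gain from adjusting.** Let r be the correlation between loss and screening ECD. Adjustment multiplies the residual variance by 1 − r², so the standardised difference becomes 0.657 / √(1 − r²). The article gives no r, so a range is shown. Power is t-based at 36 per arm.

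| r (assumed) | 1 − r² | Power, α = 0.05 | Power, α = 0.05/3 |
|---|---|---|---|
| 0 (unadjusted) | 1.00 | 78.5% | 63.1% |
| 0.1 | 0.99 | 78.9% | 63.6% |
| 0.2 | 0.96 | 80.1% | 65.2% |
| 0.365 | 0.87 | 83.9% | 70.4% |
| 0.5 | 0.75 | 88.7% | 77.6% |

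The last column is the level for three Bonferroni-corrected pairwise tests.

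**Where 0.365 comes from.** Assume a baseline SD of 300, specular error SD of 100 and proportional loss of 15%, none of which is in the article. Then cov(loss, baseline) = 100² + 0.15 × (300² − 100²) = 10,000 + 12,000 = 22,000, and r = 22,000 / (300 × 201) = 0.365.

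**Cross-check in terms of the pre/post correlation ρ.** With equal variances before and after surgery, the variance ratio of ANCOVA to change is (1 + ρ)/2. That is 0.65, 0.75, 0.85 and 0.95 for ρ = 0.3, 0.5, 0.7 and 0.9. Normal-approximation power at 36 per arm is then 93.3%, 89.6%, 85.6% and 81.6%, against 79.6% unadjusted. There is a gain throughout, but only 2 points at ρ = 0.9.

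**Chance imbalance.** The slope of loss on baseline is r × 201 / SD(baseline). One standard error of baseline difference between two arms is SD(baseline) × √(2/36). The baseline SD cancels, so the shift in the estimated effect is r × 201 × √(2/36) = 47.4 r. This is about 5 cells/mm² at r = 0.1, 9 at 0.2, 17 at 0.365 and 24 at 0.5, or 4% to 18% of the target 132.

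**Percentage loss.** I simulated the same assumed model with mean screening ECD between 2300 and 2700. Absolute loss correlates with baseline at about 0.365, and percentage loss at only about 0.15, because division removes the proportional part. At r = 0.15 the variance factor is 1 − 0.0225 = 0.978, worth about 1 point of power. Percentage loss is not noisier in this model: at mean ECD 2500, mean/SD is 1.92 against 1.87 for absolute loss.

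**The case against.** A reader might infer that the plan ignores baseline ECD and that its primary test is therefore biased or invalid. The article does not support this. The outcome is change or percentage loss from the pre-operative count, so baseline enters every patient's value. Randomisation makes the unadjusted comparison of change unbiased with correct type I error, and chance imbalance is already reflected in its standard error. The stated sample size fits that analysis.

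A reader might also infer that percentage loss shares the problem to the same degree, or that both stated outcomes should give way to postoperative ECD. Neither follows. Under the assumptions above, percentage loss depends only weakly on baseline. Regressing change on arm and baseline gives exactly the same adjusted difference as regressing postoperative ECD on them, so no stated outcome has to be demoted.

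Two further objections carry weight. The gain rests on figures that the article does not give, and at r = 0.1 it is under half a point. And the list of confounders is introduced with wording that leaves it open, in a condensed article, so a fuller plan may already contain screening ECD. That reduces the weight of the point but does not remove it: the article fixes covariate-free tests for the group comparison and names specific covariates without this one.

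**Conclusion.** The point holds as one of efficiency. Screening ECD is collected, is the baseline of the primary outcome, and is not named for adjustment, while six other variables are. The comparison as written is valid but less precise than it could be, and it carries part of any chance baseline imbalance into the estimate.

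The likely benefit for absolute change ranges from negligible to about 10 points of two-group power (78.5% to 88.7%) over assumed loss–baseline correlations of 0.1 to 0.5. For percentage loss it is probably about 1 point. These figures assume a two-sided test, 201 as the SD of ECD loss, and 36 analysed per arm. The article does not say which of the three pairwise comparisons the sample size is meant to power, so they apply to any one pair. The change is worth making because it is almost free; the trial does not fail without it.

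**What to change.** Amend the Statistical analysis section to say that ECD change will be analysed by ANCOVA (general linear model) on treatment arm with screening ECD as a covariate, and that adjusted mean differences between arms will be reported with 95% CIs. Keep percentage loss as a reported outcome and add screening ECD as a covariate there too. The same model can be fitted at each of the four visits, so the change does not depend on naming a primary visit.

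The cost is a sentence or two of wording. It needs no new measurement and no further patients, and a general linear model is available in the SPSS software already chosen. The Study status section reports that the trial was in data processing in September 2025 and does not say whether analysis had begun. The amendment should therefore be dated and recorded before any unblinded analysis. If unblinded analysis has already started, the adjusted result should be labelled as added afterwards and shown beside the planned one.
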